# Assertive outreach treatment versus care as usual for the treatment of high-need, high-cost alcohol related frequent attenders: study protocol for a randomised controlled trial

**DOI:** 10.1186/s12889-020-8437-y

**Published:** 2020-03-14

**Keywords:** Alcohol, Dependence, Frequent attenders, Assertive outreach treatment, Randomized controlled trial, Multimorbidity, High need high cost

## Abstract

**Background:**

Alcohol-related hospital admissions have doubled in the last ten years to > 1.2 m per year in England. High-need, high-cost (HNHC) alcohol-related frequent attenders (ARFA) are a relatively small subgroup of patients, having multiple admissions or attendances from alcohol during a short time period. This trial aims to test the effectiveness of an assertive outreach treatment (AOT) approach in improving clinical outcomes for ARFA, and reducing resource use in the acute setting.

**Methods:**

One hundred and sixty ARFA patients will be recruited and following baseline assessment, randomly assigned to AOT plus care as usual (CAU) or CAU alone in equal numbers. Baseline assessment includes alcohol consumption and related problems, physical and mental health comorbidity and health and social care service use in the previous 6 months using standard validated tools, plus a measure of resource use. Follow-up assessments at 6 and 12 months after randomization includes the same tools as baseline plus standard measure of patient satisfaction. Outcomes for CAU + AOT and CAU at 6 and 12 months will be compared, controlling for pre-specified baseline measures. Primary outcome will be percentage of days abstinent at 12 months. Secondary outcomes include emergency department (ED) attendance, number and length of hospital admissions, alcohol consumption, alcohol-related problems, other health service use, mental and physical comorbidity 6 and 12 months post intervention. Health economic analysis will estimate the economic impact of AOT from health, social care and societal perspectives and explore cost-effectiveness in terms of quality adjusted life years and alcohol consumption at 12-month follow-up.

**Discussion:**

AOT models piloted with alcohol dependent patients have demonstrated significant reductions in alcohol consumption and use of unplanned National Health Service (NHS) care, with increased engagement with alcohol treatment services, compared with patients receiving CAU. While AOT interventions are costlier per case than current standard care in the UK, the rationale for targeting HNHC ARFAs is because of their disproportionate contribution to overall alcohol burden on the NHS. No previous studies have evaluated the clinical and cost-effectiveness of AOT for HNHC ARFAs: this randomized controlled trial (RCT) targeting ARFAs across five South London NHS Trusts is the first.

**Trial registration:**

International standard randomized controlled trial number (ISRCTN) registry: ISRCTN67000214, retrospectively registered 26/11/2016.

## Background

Worldwide, alcohol use was the seventh leading risk factor for both deaths and DALYs (Disability-Adjusted Life year) in 2016, accounting for 2.2% of female deaths and 6.8% of male deaths. In 2016, alcohol use led to 2.8 million deaths worldwide and was the leading risk factor for premature death and disability among people aged 15–49 years. Alcohol use accounts for nearly 10% of global deaths among populations aged 15–49 years [1].

In the UK, alcohol use disorders are a major public health challenge: it is the leading cause of preventable disability in working age men [2, 3] and the third greatest risk factor for years lived with disability [4]. Deaths from liver disease have increased by over 400% since the 1970s in the UK [5], and predicted to overtake cardiovascular disease as the leading cause of death by 2021 [6].

The UK Department of Health estimates that alcohol costs the NHS in England £3.5bn per annum, 80% of which is incurred in inpatient and emergency care costs [7]. However, the wider annual costs to society in England are estimated to be considerably greater at £21bn, £11bn of which is incurred by the criminal justice system [8].

Alcohol-related hospital admissions have doubled in the last 10 years to over 1.1 m per annum in England, a quarter (337,000) of which were for conditions wholly attributable to alcohol [9]. Reducing alcohol related admissions is a key public health target and is an indicator in the Public Health Outcomes Framework [10]. High-need, high-cost (HNHC) alcohol related frequent attenders (ARFAs) are a subgroup of all patients with alcohol-related hospital admissions and are characterised by having multiple hospital admissions or attendances caused by alcohol^1^ during a relatively short time period. Whilst there is no single universal definition for an ARFA, for the purposes of this trial we defined an ARFA as someone who has had two or more admissions in any of the participating NHS trusts for at least one wholly attributable alcohol diagnoses within a 1 year period, OR; has had at least ten presentations to an emergency department in any of the participating NHS trusts within a 1 year period, OR; has at least four presentations to an emergency department in any of the participating NHS trusts within a month, OR; has been admitted at least once for a wholly attributable alcohol diagnosis and had at least four presentations to an emergency department in any of the participating NHS trusts within a 1 year period.

Previous studies show that the HNHC ARFA patient group typically have high levels of multimorbidity, including both physical and mental illness, social isolation, poor quality of life, unstable housing or homelessness, high criminal justice involvement, unemployment and living on benefits [11]. Notably, they either have poor or no engagement with existing specialist alcohol treatment services. Their Accident and Emergency Department (A&E) attendance is frequent, often due to not being registered with a General Practitioner (GP), and they have frequent emergency hospital admissions to both acute and mental health beds. Qualitative research has also identified that as a group ARFAs experience high levels of stigma and social exclusion [12].

An intensive assertive outreach treatment (AOT) intervention has been developed to target the patients who have the highest alcohol related hospital attendance. AOT is based on a model of community service provision originally designed for people with severe mental illness (SMI) and was first pioneered by the work of Stein and Test (1980) [13]. AOT emphasises active engagement over an extended period [14, 15] and has several features which distinguish it from usual care, including: (i) rapid access to services, (ii) a small caseload, (iii) a high ratio of community to office-based appointments, (iv) assertive engagement (e.g. with multiple attempts) and (v) a shared care approach, with care coordinators working within a multidisciplinary team that meets frequently [16, 17]. In adult mental health care, AOT (sometimes also referred to as Assertive Community Treatment) is an extensively researched and widely used model of care for treating difficult to engage patients with severe and enduring mental illness. AOT and its elements have also been used in the treatment of alcohol dependence [18, 19] which clinically, like severe and enduring mental illness, also often presents as a chronic relapsing disorder with high public health costs [20–25]. An AOT model implemented with alcohol dependent patients, demonstrated significant reductions in alcohol consumption and use of unplanned NHS care, as well as increased engagement with alcohol treatment services, compared with patients receiving care as usual [14]. A national survey of AOT services for ARFAs in 2017 [21] found 76 services across England offering AOT for ARFAs between December 2015 and June 2016. The majority included a multi-disciplinary team and offered extended support including advice on housing, mental and physical health in addition to alcohol treatment, however there was considerable variation amongst the models of care delivered and no previous RCTs have evaluated their clinical effectiveness and cost-effectiveness.

While AOT interventions are more costly per case than current standard care in the UK, the rationale for targeting HNHC ARFAs is that they incur a disproportionately high amount of the overall alcohol burden on the NHS. Hence the potential savings to the NHS, as well as to wider social and criminal justice services, from a successful intervention outcome are greater than other less intensive interventions for less complex patients.

## Methods

### Aim

This randomised controlled trial will assess the clinical and cost-effectiveness of care as usual (CAU) plus AOT compared with CAU alone for adults who have frequent alcohol related admissions.

### Objectives

To conduct a randomised controlled trial of CAU + AOT versus CAU in a sample of alcohol related frequent attenders in five NHS trusts in South East London.To evaluate the effectiveness and cost-effectiveness of CAU + AOT versus CAU alone in ARFAs to acute and mental health inpatient care.To describe the characteristics and health and social care needs of ARFAs.To identify potential mechanisms of action of AOT and identify patient sub-groups for whom AOT is more effective.

### Primary hypothesis

CAU + AOT will be more effective than CAU alone in increasing the proportion of days abstinent from alcohol, measured by the Time Line Follow Back (TLFB) form 90, at 12 months follow-up.

### Secondary hypotheses

CAU + AOT will be cost-effective compared with CAU alone at 12 months follow-up.CAU + AOT will reduce unplanned health care utilisation including admissions to Emergency Departments (ED) and acute and mental health inpatient care compared to CAU alone.CAU + AOT will increase engagement with specialist addiction and recovery services compared to CAU alone.Addiction treatment engagement, readiness to change and therapeutic alliance will moderate treatment effectiveness.

### Assertive outreach treatment intervention

Patients in the intervention arm of the study will receive AOT in addition to usual care. AOT will incorporate the following elements [14]:
(i)Each AOT practitioner should have a maximum caseload of 15 AOT patients.(ii)Care provided by a multidisciplinary team (including psychiatrists, community addiction nurses, substance use disorder specialists, community support workers).(iii)Frequent and regular contact between practitioner and patient (at least once a week predominantly in patients’ homes and local community settings).(iv)Assertive engagement – persistent and repeated attempts by the practitioner to make contact, with the emphasis being on maintaining contact and building relationships.(v)Content of sessions will focus on both health and social care needs – including accommodation, leisure, occupation, and physical and mental health, with an emphasis on a patient-led agenda.(vi)Flexibility – practitioners should work flexibly with patients’ goals and include those which are less related to the addiction. The AOT model has abstinence from alcohol as its ultimate clinical goal. However, whilst all treatment aspires to achieve full recovery, it can be an unrealistic short-term goal for more severely dependent drinkers with complex social support needs plus multiple comorbidities, in which case a reduction in harmful drinking will be a more realistic goal.(vii)Openness – practitioners explain their role and aims in care planning and in visits.(viii)Practitioners operate more broadly than in their usual professional roles to provide a wide range of support to patients.(ix)Extended care – AOT will be provided for a period of 1 year during which patients will be introduced to other existing community services who will ultimately provide them with on-going support in the longer-term.

AOT will be used to proactively engage with ARFA patients, to assess their physical and mental health and wider social needs, then to develop shared treatment goals, and to facilitate and coordinate engagement with the relevant care and support to address their multiple presenting needs. The AOT will mainly take place either in the patient’s home or local community settings. A treatment manual has been developed by the research team as part of a previous clinical trial [11].

### Training

All staff who will be delivering the AOT service will participate in a training programme, focusing on:
Key features of AOT and how it should be delivered in the context of alcohol-related frequent attenders, including techniques to maximise engagement.Overview of the research trial, inclusion and exclusion criteria, obtaining consent, the assessment tools being used in the trial, maintaining contact logs.Safety whilst working in the community.

In addition, each member of staff will spend a day shadowing mental health assertive outreach staff participating in community and home visits with patients. This will also provide staff with the opportunity to ask questions around practical issues associated with delivering AOT.

### Control intervention

All participants in the control arm of the study will receive CAU i.e. routine clinical practice, so that the hypothesis that CAU + AOT is more effective than CAU alone can be tested. CAU typically involves treatment of presenting physical or mental health problems and referral to specialist addiction services for ongoing help with alcohol related problems. Patients receiving CAU have access to medical detoxification, psychological interventions targeting drinking behaviour and aftercare, which are usually provided by specialist addiction services. But in contrast to AOT, the emphasis will be on the patient’s own motivation to engage with available services. Specialist input from addictions psychiatry, clinical psychology and social work may also be a part of CAU but the assertive and regular nature of contacts in AOT does not feature.

### Intervention fidelity

Prior to delivering AOT all staff will undergo training as outlined above. Practitioners will attend regular weekly multidisciplinary clinical meetings and regular individual and group supervision to ensure that the intervention is being delivered in a consistent manner by all practitioners, in line with the characteristic features of AOT. Staff providing care to patients will be asked to complete a log of the contacts they have with patients and the care provided. This will include the nature of the contact (face-to-face meetings, telephone calls, text messages and emails), setting (home, community, clinical), the focus of the contact (mental health, physical health, housing, finance etc), duration of the contact, and the member of staff involved.

### Participants

#### Inclusion criteria

i)Age 18 years or over.ii)Able to understand English sufficiently well to obtain informed consent and complete the assessment instruments.iii)has had two or more admissions in any of the participating NHS trusts for at least one wholly attributable alcohol diagnoses within a 1 year period, OR; has had at least ten presentations to an emergency department in any of the participating NHS trusts within a 1 year period, OR; has had at least four presentations to an emergency department in any of the participating NHS trusts within a month, OR; has been admitted at least once for a wholly attributable alcohol diagnosis and had at least four presentations to an emergency department in any of the participating NHS trusts within a 1 year period.iv)International Classification of Diseases version 10 (ICD-10) diagnosis of alcohol dependence.v)Willing to provide informed consent to participate in the trial.vi)A resident of Lambeth and Southwark and admitted to one of the five participating NHS Trusts.

#### Exclusion criteria

i)Unable to give informed consent.ii)Experiencing severe mental of physical illness likely to preclude active participation in the treatment or research follow up.iii)Already in receipt of assertive outreach services or participation in another trial.iv)Has a severe cognitive impairment as determined by Mini Mental State Examination score of ≤10 [22].v)Has a history of violence to staff or is registered under multi-agency public protection arrangements (MAPPA).vi)Dependence on opiates or stimulants.vii)Street homeless or has no recourse to public funds.

### Identification and recruitment of potential participants

The AOT clinical team will work with informatics teams in the five NHS trusts (King’s College Hospital (KCH)-, Guy’s and St Thomas’ (GST)-, South London and Maudsley (SLaM)- and St George’s Healthcare (STG)- NHS Foundation Trusts; and Lewisham and Greenwich (LGT) NHS Trust) to identify HNHC ARFA based on primary or secondary clinical diagnoses of alcohol related admissions and number of admissions or emergency department attendances in the previous 12 months. This will also include the use of the clinical research information system (CRIS) within SLaM. The clinical team will also have access to electronic clinical records and discuss potentially eligible patients with clinicians in inpatient units in the five trusts, and the Alcohol Care Teams at KCH, STG and GST, to identify additional patients who meet the study criteria but are not captured by diagnostic criteria in electronic records.

Once potentially eligible patients have been identified, they will be contacted by the AOT clinical team and assessed for eligibility and informed about the potential to participate in the trial. They will be given the Patient Information Sheet and the trial will be explained verbally. Patients will be encouraged to ask questions or consult carers, relatives or their GP. If willing to proceed, eligible patients will be introduced to a member of the research team who will again explain the trial, confirm the patient’s eligibility, and obtain informed consent. The minimum period of time between informing the patients of the trial and obtaining consent will be 24 h. Patients unwilling to take part will be offered the standard CAU, including referral to local specialist addiction services.

Patients who provide informed consent will undergo a baseline research assessment conducted by the research team and will be randomised using an electronic trial management tool. In order to maintain blinding of researchers, the treatment allocation will be provided only to the AOT clinical team who will then initiate AOT treatment or referral to specialist addictions services as appropriate.

### Baseline assessment

(i)Socio-demographic information: age, sex, ethnicity, marital status, living arrangement, children, living arrangements of children, education.(ii)Drinking in the previous 90 days – TLFB 90I [23]. The TLFB is a validated interview method to measure alcohol consumption in the previous 90 days and is the gold standard outcome measure in alcohol treatment research. Percentage days abstinent, units of alcohol per drinking day (1 UK unit = 8 g alcohol), time to first alcoholic drink, relapse to any drinking and relapse to heavy drinking (8+/6+ units for males/females on a single occasion) will be computed.(iii)History of drug use – TLFB.(iv)Alcohol related problems - Alcohol Problems Questionnaire (APQ) [24]. The APQ is a validated 46-item questionnaire assessing potential problems with psychological, physical, social, legal, employment, relationships and parenting that may be experienced due to alcohol.(v)Severity of alcohol dependence - Severity of Alcohol Dependence Questionnaire (SADQ) [25]. The SADQ is a validated 20-item self-complete questionnaire containing items representing five domains of the alcohol dependence syndrome: (i) physical withdrawal signs (ii) psychological withdrawal signs (iii) withdrawal relief drinking (iv) tolerance (v) reinstatement following a period of abstinence.(vi)Health related quality of life – EuroQol 5 dimensions 5 levels (EQ-5D-5 L) [26]. The EQ-5D-5 L consists of five dimensions (mobility, self-care, usual activities, pain/discomfort and anxiety/depression) scored on five levels (no problems, slight problems, moderate problems, severe problems and extreme problems). The EQ-5D-5 L is an extension of the original 3-level EQ-5D and has been shown to be valid [27].

This version of EuroQol measure of health-related quality of life capable of generating quality adjusted life years (QALYs) for use in economic evaluations.
(vii)Health Related Quality of life – Short-form-12 (SF-12) [28]-a 12 item subset of Short form-36, for measuring self-reported health related quality of life.(viii)Motivation to change - Readiness to Change - Treatment version [29]- a 12 item questionnaire used to assess the subject’s stage of change.(ix)Social network involvement - Important People and Activities Inventory [30]. This measure gathers information regarding general and alcohol-specific types of support. This scale contains 11 indices which in combination create a summary measure for predicting alcohol use,(x)Resource use – Adult Service Use Schedule (AD-SUS) [31] The AD-SUS is a resource use measure designed for and applied to mental health populations, including drug and alcohol populations.

### Follow up assessments

Six and twelve months after randomisation, all participants will be followed up (see Fig. 1). A research worker, blind to treatment allocation, will arrange a convenient time to meet with the participant. Baseline measures (items i-x above) will be repeated in addition to:
(xi)Therapeutic relationship – Scale to assess therapeutic relationship (STAR) [32] completed at 12 months follow-up. Therapeutic relationship (or alliance) has been found to predict clinical outcome across a range of mental disorders including alcohol dependence. This will be used as an additional process measure to assess the impact of therapeutic relationship on medication adherence and clinical outcome.

**Fig. 1 Fig1:**
[figure not shown]
SPIRIT diagram for the schedule of enrolment, interventions, and assessments

Maintaining the researcher’s blindness to treatment allocation is an acknowledged problem in psychosocial intervention trials in comparison to placebo controlled medication trials. In order to reduce the risk of participants inadvertently revealing the treatment allocation, researchers will advise participants not to discuss their ongoing treatment arrangements or the identity of their key worker or service and will conduct the TLFB measure before discussing service utilisation as in a previous trial [11].

### Randomisation and blinding

Randomisation to one of the two treatment arms will take place after consent and baseline data have been collected, by a remote electronic allocation system. Once baseline data has been submitted on the electronic device by the researcher, the system will email the randomised allocation to a member of the clinical team. The researchers will be blind to the allocated intervention throughout the trial. The online system will be developed and maintained by Codeface Ltd. Randomisation will be stratified by site and severity of alcohol dependence (< = 30 and > 30), as measured by the Severity of Alcohol Dependence Questionnaire (SADQ).

### Sample size and power

The primary outcome of the RCT is percent days abstinent using validated Time-Line Follow-Back (TLFB) interview method over a 90-day reference period at 12 months post-recruitment, which is the gold standard in alcohol treatment research. Similar studies have used effect sizes of 0.3–0.5 in their sample size calculations [14]. We propose using an effect size of 0.4, alongside type 1 error rate, α = 0.05 and type 2 error rate, β = 0.8 and using a two-sided test. This indicates a sample size of 64 patients each in intervention and control group included in the analysis at the primary end-point. In order to address potential loss to follow-up we have incorporated a loss of 20%, larger than previous studies such as ACTAD that had a loss to follow-up of 7% at 12 months but smaller than UKATT [33] that has a 28% loss at 12 months. This inflates the required sample size at recruitment to 80 in each group a total of 160 at baseline with the expectation that at least 64 in each group, a total of 128, will be followed up at 12 months.

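### 64 analysed per group gives 80% power for an effect size of 0.5, not the stated 0.4, where unadjusted power is about 61%

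*Protocol article*

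**What the plan says.** The calculation is in the Protocol article, Sample size and power. The authors cite precedent, "Similar studies have used effect sizes of 0.3–0.5 in their sample size calculations", and choose a value inside that range: "We propose using an effect size of 0.4". The remaining inputs are "type 1 error rate, α = 0.05", "type 2 error rate, β = 0.8" and "using a two-sided test". The result follows directly: "This indicates a sample size of 64 patients each in intervention and control group included in the analysis at the primary end-point". An allowance of 20% for loss to follow-up takes this to 80 per group and 160 in total, with 128 expected at 12 months. The Abstract repeats the total: "One hundred and sixty ARFA patients will be recruited", with equal allocation.

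The section gives no standard deviation, no covariate correlation and no other variance reduction. Under Statistical analysis, the primary comparison is an analysis of covariance whose named covariates are the stratification variables, SADQ and site.

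**The concern.** The section states every input of a standard two-group calculation and then a result that does not follow from them. The figure 64 is the familiar answer for a standardised difference of 0.5 with 80% power and two-sided alpha of 0.05, and 0.5 is the top of the range cited in the same section. A second slip sits beside it: 0.8 is called the type 2 error rate, although it must be the power.

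This calculation is the article's only justification for the trial's size, and it supports the primary hypothesis on days abstinent. If the true effect is the planned 0.4, readers would take a non-significant result as a miss by a trial with 80% power when the chance of a miss is nearly double the intended 20%. Assertive outreach could then be dismissed for this population on a false premise.

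**Working it through.** **Inputs** (Protocol article, Sample size and power; equal allocation from the Abstract)
- Effect size d = 0.4, read as a standardised mean difference
- Two-sided alpha = 0.05, so z = 1.960
- Power 0.80 (reading 0.8 as power), so z = 0.842
- Loss to follow-up 20%

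**Formula.** Normal approximation: n per group = 2(z₁₋α/₂ + z₁₋β)² / d². The exact t-test version adds about one patient per group.

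**Trying to reproduce 64.** 2 × (1.960 + 0.842)² = 15.70.

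| d | Normal approximation | t-test | Analysed per group (t-test, rounded up) |
|---|---|---|---|
| 0.3 | 15.70/0.09 = 174.4 | 175.4 | 176 |
| 0.4 | 15.70/0.16 = 98.1 | 99.1 | **100** |
| 0.5 | 15.70/0.25 = 62.8 | 63.8 | **64** |

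The stated 64 is reproduced at d = 0.5 and not at d = 0.4.

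**Other readings at d = 0.4**
- One-sided alpha of 0.05: 2 × (1.645 + 0.842)²/0.16 = 77.3, so 78.
- Beta of 0.8 taken literally (power 20%): 2 × (1.960 − 0.842)²/0.16 = 15.6, so 16; the t-test gives 16.5, so 17.
- Power 90%: 132.

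None gives 64.

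**The loss step.** 64/(1 − 0.20) = 80 per group, 160 in total. This is correct, so the mismatch arises before it. Starting from 100, the same step gives 100/0.80 = 125 per group, 250 in total.

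**Power at d = 0.4.** Normal approximation with 64 per group: 0.4 × √(64/2) − 1.960 = 2.263 − 1.960 = 0.303, and Φ(0.303) = 0.619. The t-test figures are:

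| Analysed per group | Power at d = 0.4 | Effect detectable with 80% power |
|---|---|---|
| 64 | 61.2% | 0.50 |
| 80 (no loss) | 71.0% | 0.45 |

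With 64 per group, power at d = 0.5 is 80.1%. The type 2 error at 0.4 is 100% − 61.2% = 38.8%.

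**Could covariate adjustment explain 64?** Adjustment for covariates that correlate r with the outcome multiplies n by (1 − r²). To go from 100 to 64 needs 1 − r² = 0.64, so r = 0.6. The document gives no r. Over assumed values, with 64 per group and d = 0.4 (normal approximation):

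| Assumed r | Power |
|---|---|
| 0 | 62% |
| 0.3 | 66% |
| 0.4 | 69% |
| 0.5 | 74% |
| 0.6 | 81% |

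**The case against.** The arithmetic mismatch is not in dispute. What can be said for the plan is this.

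- **The slip may be in the effect size.** Everything from 64 onward is consistent (80, 160, 128), and 0.5 lies within the cited range. This stands: the document does not show whether 0.4 or 64 is wrong. The sentence is false as written either way.
- **The 61% is for an unadjusted comparison, and the plan is an analysis of covariance.** This also stands in part: prognostic covariates would raise power, so 61% should be labelled unadjusted. It does not close the gap. The named covariates are SADQ and site, baseline days abstinent is not among them, and assumed correlations up to 0.5 leave power at 74% or less. An undeclared adjustment would also have to land, by coincidence, on the unadjusted answer for 0.5.
- **Confidence intervals will be reported and the sample can no longer change.** True: the intervals will show the precision achieved, and the article says analysis is ongoing. This makes the point a reporting correction. It does not make the power claim correct.
- **The beta label is an obvious slip.** Agreed. It does not explain 64 and adds little weight, but it sits in the same sentence and is easily corrected.

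**Conclusion.** The concern holds. On the article's own inputs the requirement is 100 analysed per group (99 by the normal approximation), not 64, and 64 is the answer for 0.5. If 0.4 is the intended target, the planned trial has about 61% unadjusted power instead of 80%, and a design matching the text would recruit 250 instead of 160. If 0.5 was intended, the sample size is right and the stated effect size is wrong.

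This rests on reading the effect size as a standardised mean difference, reading 0.8 as power, equal allocation, and no variance reduction, since none is stated. Only a covariate–outcome correlation of about 0.6 would reconcile 0.4 with 64, and nothing in the document supports assuming one.

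**What to change.** Keep 160 and correct the statement in Sample size and power:
- Give the type 2 error rate as beta = 0.2 (power 80%).
- State that 64 analysed per group gives 80% power for a standardised difference of 0.5, and about 61%, unadjusted, for 0.4. Both statements are true whichever figure was the slip.
- Report which inputs the calculation actually used. A covariate correlation should not be brought in afterwards to justify 0.4.

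The cost is wording only. No patients are added and the analysis is unchanged; the price is a less favourable power claim, which should carry through to the results paper.
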